### Primary and secondary objectives

The primary objective of this study is to quantify the sensitivity of an adaptive surveillance-response approach for its ability to detect *S. haematobium* infected individuals in low-prevalence areas to trigger an appropriate intervention response. The primary outcome variable will be the number of *S. haematobium* infected individuals detected and reported through the surveillance approach divided by the number of positive individuals in the population as extrapolated from the cross-sectional surveys, i.e. the mean sensitivity of the surveillance-response approach determined over 3 years.

Secondary outcome analyses will cover additional performance parameters of the surveillance approach, as defined by WHO [45]. Moreover, we will assess the impact of multi-disciplinary interventions in hotspot areas, as well as the coverage of test-and-treat activities in low-prevalence areas and of MDA in hotspot areas. Other secondary outcomes will include the accuracy of several diagnostic approaches and micro-mapping of characteristics of the study shehias, including the number and location of schools, madrassas (Islamic schools), and health facilities, the number and location of water bodies and the abundance of intermediate host snails of the genus *Bulinus*.

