#### Intervention packages and data collection in hotspot implementation units

In the hotspot IUs, where a considerable part of the population is still infected with *S. haematobium*, we will implement a multi-disciplinary intervention package including MDA, snail control and behaviour change communication activities.

Large-scale MDA with praziquantel is the corner stone for the control and prevention of morbidity due to schistosomiasis [3, 5]. Praziquantel treatment is administered without prior diagnosis to large parts of the population living in endemic areas. In our hotspot IUs, MDA will be conducted at least annually in communities and schools by the Zanzibar NTD Programme. In communities, community drug distributors trained by the MoHSWEGC will visit all households in a door-to-door approach and offer to treat children aged 4 years or older with praziquantel (40 mg/kg) if they do not receive treatment in schools. Moreover, they will offer praziquantel to all adults that are eligible for treatment according to national treatment guidelines. In schools, praziquantel (40 mg/kg) will be provided to all children present at the day of treatment by teachers and staff of the Zanzibar NTD Programme using a dose pole [50]. The intake of tablets will be directly observed. Treatment coverage will be reported by the Zanzibar MoHSWEGC based on reports from their staff, community drug distributors, and teachers. Moreover, we will conduct our own post-treatment coverage surveys in line with the annual cross-sectional parasitology surveys in the hotspot communities and schools. When invited to submit a urine sample for annual monitoring, individuals enrolled in the survey will also be invited to respond to an ODK questionnaire, asking if they have received and swallowed the drugs provided in the MDA treatment round preceding the survey.

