### Statistical methods

To analyse the primary outcome, we define the sensitivity of the surveillance system as the proportion of cases detected:$${\text{SE}} = {\text{N}}_{{{\text{inf detected by surveillance}}}} / {\text{N}}_{{{\text{inf}}}}$$

The total number of infected persons is unknown but will be estimated from the cross-sectional surveys as:$${\text{N}}_{{{\text{inf}}}} = {\text{ P}}_{{{\text{school}}}} *{\text{ N}}_{{{\text{school}}}} + {\text{ P}}_{{{\text{non}} - {\text{school}}}} *{\text{ N}}_{{ {\text{non}} - {\text{school}}}}$$whereby prevalences (P) and corresponding confidence intervals are estimated via generalized estimating equations for binary data with independent correlation structure to account for correlation within clusters.

The prevalence and intensity of *S. haematobium* infections will be calculated by different diagnostic approaches used in the annual cross-sectional surveys. Intensity of infection will be classified into light (< 50 eggs/10 ml urine) and heavy (≥ 50 eggs/10 ml urine) according to thresholds provided by the WHO for urine filtration results [3].

The timeliness of case notification and reactive intervention will be assessed by recording the time needed from diagnosis to treatment, from diagnosis to follow-up of *S. haematobium* positive individuals and test-and-treat of their household members, and from diagnosis to reactive snail control.

The acceptability of the surveillance-response approach will be assessed by a mixed methods approach based on the results of questionnaires run in parallel to test-and-treat approaches in low-prevalence shehias.

The coverage of test-and-treat activities will be calculated by assessing the number of people who were targeted by test-and-treat activities in relation to the total population.

MDA coverage will be calculated by assessing the number of people reporting in the cross-sectional surveys that they received praziquantel during the last MDA in relation to the total number of participants in the cross-sectional surveys.

MDA compliance in hotspot areas will be calculated by assessing the number of people reporting in the cross-sectional surveys that they have taken praziquantel as recommended, in relation to the total number of participants in the cross-sectional surveys.

The impact of snail control will be determined by assessing the snail abundance and number of intermediate host snails at each HWCS identified over time during regular snail surveys.

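### MDA compliance is divided by all survey participants rather than by those who received the drug, so the figure read alone mixes delivery with swallowing

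*Protocol article*

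**What the plan says.** Two adjacent sentences in the Statistical methods section of the protocol article define the MDA measures. Coverage is "the number of people reporting in the cross-sectional surveys that they received praziquantel during the last MDA in relation to the total number" of survey participants. The next sentence defines compliance in hotspot areas as "the number of people reporting in the cross-sectional surveys that they have taken praziquantel as recommended, in relation to the total number of participants" in those surveys. Both measures thus have all survey participants below the line. The compliance sentence names hotspot areas and the coverage sentence does not. The Primary and secondary objectives section does tie MDA coverage to hotspots, since it lists "the coverage of test-and-treat activities in low-prevalence areas and of MDA in hotspot areas".

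The section on intervention packages in hotspot implementation units describes the data source, a questionnaire to enrolled individuals "asking if they have received and swallowed the drugs provided in the MDA treatment round preceding the survey". It also shows that not every participant will have been given tablets. Of the community drug distributors it says that "they will offer praziquantel to all adults that are eligible for treatment according to national treatment guidelines", and in schools the drug goes to children present on the treatment day. The survey itself is wider: it admits consenting residents aged 4 years or older who give enough urine, whether or not they could be treated.

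No other part of the article defines compliance with recipients as the denominator.

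**The concern.** Compliance normally asks whether people who were given a drug took it. A participant who was ineligible, was away, or was not reached by a distributor had nothing to comply with. Under the written definition that person stays in the denominator, cannot enter the numerator, and so lowers reported compliance.

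A low figure would then naturally be read as unwillingness to swallow the tablets, although the cause might be incomplete distribution. The two problems call for different programme responses. The Discussion treats good coverage as key to success and expects the results to guide future strategic plans, so a reader may well act on the compliance figure.

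**Working it through.** The article states no coverage or compliance value, so there is none to reproduce. The one related figure is the yearly survey total: 20 shehias × (140 schoolchildren + 250 community members) = 20 × 390 = 7,800, which matches the Sample size section. That section plans on 15 low-prevalence shehias, which leaves 5 hotspots and 5 × 390 = 1,950 hotspot participants.

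**Algebra.** Let N be the hotspot participants, R those who report receiving praziquantel in the last MDA, and T those who report taking it as recommended, with T ≤ R ≤ N.

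- Coverage = R/N
- Compliance as written = T/N = (R/N) × (T/R) = coverage × share of recipients who swallowed
- Compliance among recipients = T/R

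Since T ≤ R, T/N cannot exceed R/N. T/N equals T/R only if R = N, that is, if every participant received tablets.

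**Illustration.** The receipt rate r = R/N and the swallowing rate s = T/R are not in the article and are assumed here. With s = 0.95 and N = 1,950:

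| r (coverage) | R | Compliance as written, r × s | T/R | Gap, points |
|---|---|---|---|---|
| 60% | 1,170 | 0.60 × 0.95 = 57.0% | 95% | 38.0 |
| 70% | 1,365 | 0.70 × 0.95 = 66.5% | 95% | 28.5 |
| 90% | 1,755 | 0.90 × 0.95 = 85.5% | 95% | 9.5 |

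In general the gap is s − r × s = s × (1 − r). Over r from 0.50 to 0.90 and s from 0.80 to 1.00 it runs from 0.80 × 0.10 = 8 points to 1.00 × 0.50 = 50 points.

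**Can the swallowing rate be recovered?** Take two contrasting cases.

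- r = 0.60, s = 1.00: coverage 60%, compliance as written 60%, ratio 60/60 = 100%.
- r = 1.00, s = 0.60: coverage 100%, compliance as written 60%, ratio 60/100 = 60%.

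The compliance figures are identical, but the pairs differ and their ratio returns s in each case.

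**What if the coverage sentence is taken literally?** Suppose coverage were computed over all 7,800 participants, with MDA in the 5 hotspots only. At r = 0.60 it would be 1,950 × 0.60 / 7,800 = 15%, and at r = 0.80 it would be 20%. Hotspot compliance as written, with s between 0.90 and 1.00, would be 54% to 80%. The cap then fails, and so does the division: 54/15 = 3.6, which cannot be a proportion. The objectives point to the hotspot reading, but the coverage definition itself should say so.

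**The case against.** The strongest reply is that nothing is lost. Coverage is reported beside compliance, and over the same participants their ratio is exactly the swallowing rate. A reader might infer that the two measures cannot tell poor delivery from poor swallowing. The documents do not support that: the two cases above give the same compliance figure but different pairs. This part of the reply stands, on condition that both measures use hotspot participants.

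A reader might also infer that compliance can never exceed coverage. That holds only with a common set of participants, which the coverage sentence does not spell out.

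Further points on the other side:

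- The share of all participants who took the drug is a legitimate quantity, correctly computed, so much of the fault is in its name. This stands, and the fix keeps that quantity under another name.
- The article nowhere says that the two measures are meant to separate delivery from refusal. The objectives list MDA coverage but not compliance, and no threshold or test depends on compliance. Shehias are classified by prevalence. This stands and limits the consequence.
- School intake is directly observed, so receipt and swallowing should nearly coincide there and the recipients-only ratio may sit near 100%. That is fair, but it equally means that the written measure would almost repeat coverage in schools.
- Dividing by receipt removes people who refused tablets at the door. Dividing by people offered the drug would include them, but the article describes questions on receipt and swallowing only. So it does not support a claim that an offered-based measure is available without new data.

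None of this makes all participants the right denominator for a figure called compliance.

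**Conclusion.** The point holds as a denominator and labelling error in a secondary descriptive measure. Compliance as written is coverage multiplied by the swallowing rate, and it scores people who never received tablets as non-compliant. Read alone, it misleads.

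The size depends on the receipt rate. The reported 57% to 86% against 95% rests on assumed rates and illustrates the mechanism; it does not predict this study's results. The cap at coverage and the recovery by division both assume that the two measures share the same hotspot participants and that taking the drug as recommended implies having received it in the last round. The objectives and the questionnaire description support both assumptions. The sensitivity of the surveillance approach, which is the primary outcome, does not use this measure and is unaffected.

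**What to change.** In the Statistical methods section:

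1. Define MDA compliance as hotspot participants who report swallowing praziquantel as recommended, divided by hotspot participants who report receiving it in the last MDA round.
2. Report those who swallowed it over all hotspot participants as a separate line, named treatment coverage or uptake.
3. State that MDA coverage is also taken over hotspot participants, in line with the objectives.
4. Note that a receipt denominator does not capture people who were offered tablets and refused them.

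The cost is a few changed sentences and one changed denominator. The article describes receipt and swallowing as both asked, so no new data should be needed. The questionnaire is not shown, so the team should confirm that the two answers are recorded separately. Measuring refusal would need an item on offer, which the article does not describe.

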**Fig. 4 Fig4:**
[figure not shown]
Interventions and components of surveillance-response activities implemented in low-prevalence shehias of the SchistoBreak study in Pemba, Tanzania

As starting point for risk-based surveillance activities, we will select the largest public primary school in each shehia, and a madrassa with a minimum of 50 children that is located at maximum 500 m away from a water body and the farthest away from the primary school to gain a differentiated picture about the *S. haematobium* micro-epidemiology at school level in each shehia [12].

For active case finding, we will visit the selected schools at least once per year, register all children of the grades 3–5 present at the first day of the visit, and provide them with an ICF for their parents to sign. Additionally, every child aged 12 years or older will be invited to sign an assent form on their own behalf. The next day, upon submission of the signed ICF and assent forms, each child will receive a plastic container and be invited to produce its own urine sample. The submitted urine samples will be examined at the point-of-care (PoC) in the school using reagent strips (Haemastix; *Siemens* Healthcare Diagnostics AG; Zürich, Switzerland) and additional PoC tests if available. Haematuria-positive and/or *S. haematobium* infected children will be treated with praziquantel (40 mg/kg using a dose pole) on the day of or day after examination.

For reactive case detection in the days following the active case detection in schools, children tested positive in the schools will be asked to show a member of the study team their house of residence and the water bodies they are using for household chores or leisure activities. Household members of the infected child who are present at the time of the visit will be offered PoC testing with reagent strips (and additional PoC tests if available) and praziquantel treatment if diagnosed positive.

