Finally, good coverage will be key for the success of our intervention approaches. In the low-prevalence IUs, surveillance-response activities will start in schools and be extended in a snowball system to households of *S. haematobium*-infected individuals and the water bodies they use. In hotspot IUs, MDA will be conducted in communities and target all eligible household members in a shehia. Schools, including not only primary schools, but also nurseries, secondary schools and madrassas, will be used as additional venues for MDA to reach as many children as possible. Snail surveys will be conducted repeatedly and multiple times per year at the HWCSs of all known water bodies in hotspot shehias. If *Bulinus* is detected in a water body, the HWCSs will be sprayed with niclosamide. Behaviour change communication including trainings in interactive teaching methods about schistosomiasis for teachers and their equipment with schistosomiasis teaching material will target all public, private and religious schools in the hotspot shehias. Public outreach days (Kichocho days) will be conducted in at least two schools per shehia and reach not only the majority of teachers and children attending the school but additional visitors from the communities. Striking health education messages and knowledge about the transmission and prevention of schistosomiasis will be transferred. Two laundry platforms per shehia will be constructed in close collaboration with the community near clean water sources to provide the communities with safe options for washing clothes. However, the implementation and coverage of the surveillance-response activities in low-prevalence IUs and the intervention package in hotspot IUs will be limited by time, costs and logistical feasibility and require careful and adaptive planning and implementation throughout the study period.

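### MDA compliance is divided by all survey participants, so as defined it measures effective coverage; the two neighbouring coverage definitions also need tighter wording (minor)

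*Protocol article*

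**What the plan says.** Three process measures are defined in consecutive sentences of Statistical methods.

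- **MDA coverage:** the number of survey participants reporting that "they received praziquantel during the last MDA in relation to the total number of participants in the cross-sectional surveys".
- **MDA compliance in hotspot areas:** the number reporting that "they have taken praziquantel as recommended, in relation to the total number of participants in the cross-sectional surveys".
- **Test-and-treat coverage:** "the number of people who were targeted by test-and-treat activities in relation to the total population".

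The section on intervention packages in hotspot implementation units describes the source of the MDA data. Survey participants answer a questionnaire "asking if they have received and swallowed the drugs provided in the MDA treatment round preceding the survey", so receipt and swallowing are both recorded. The same section limits community MDA in adults to those eligible under national guidelines.

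Primary and secondary objectives lists "the coverage of test-and-treat activities in low-prevalence areas and of MDA in hotspot areas" among the matters to be assessed. Compliance is not named there.

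**The concern.** Compliance ordinarily means the share of people given a drug who take it. With all survey participants in the denominator, a person whom no distributor visited lowers the figure exactly as a person who received tablets and did not swallow them. So does a participant who was not eligible. The number printed as compliance would fall whenever distribution fell short, even if every recipient swallowed the tablets.

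This affects interpretation. The Discussion calls good coverage key to the success of the approaches, and it concedes that a statistically significant change in prevalence will most likely not be shown. Process measures will therefore carry much of the explanation if transmission persists. A low figure labelled compliance points towards reluctance to take the drug, when the cause may be delivery.

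The test-and-treat definition raises a smaller question of the same kind: whether people approached but never tested count as covered.

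**Working it through.** **1. The plan's own figure.** The article gives no value for MDA coverage or compliance. The only figure bearing on coverage is in Sample size: about 12,150 people tested per year, ca. 20% of the population.

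- Schools: 15 × 450 + 15 × 50 = 7,500
- Households: 15 × 10 × 5 = 750
- Water-contact stalls: 15 × 10 × 10 = 1,500
- Health facilities: 20 × 12 × 10 = 2,400
- Total: 12,150. Over 15 × 4,000 = 60,000 inhabitants this is 20.25%.

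Both stated figures are reproduced. The numerator is people tested, and the denominator is the low-prevalence shehias.

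**2. Compliance as defined.** Let n be the survey participants, r those who received the drug, and s those who took it as recommended, all of whom are among r.

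- Coverage = r/n
- Compliance as written = s/n = (r/n) × (s/r)
- Compliance among receivers = s/r

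So s/n cannot exceed r/n, and it moves with delivery. The values below are assumptions, because the article gives none.

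| Received (r/n) | Swallowed among receivers (s/r) | Compliance as written (s/n) |
|---|---|---|
| 60% | 100% | 60% |
| 60% | 95% | 57% |
| 80% | 90% | 72% |
| 90% | 95% | 85.5% |

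Over assumed receipt of 50% to 90% and swallowing of 80% to 100%, the figure as written runs from 0.50 × 0.80 = 40% to 0.90 × 1.00 = 90%. The conditional value runs from 80% to 100%.

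**3. *Targeted* against *tested*.** For active case finding in schools, the team will "register all children of the grades 3–5 present at the first day of the visit"; only children who then return signed forms and provide urine are tested. Elsewhere the article uses the verb for people intended to be reached: in the Discussion, "MDA will be conducted in communities and target all eligible household members in a shehia". Read that way, the numerator is larger than the number tested.

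To see by how much, hold the number tested at 12,150.

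- Losses in schools only, using the 20% drop-out that the plan allows for its school survey: 7,500/0.80 = 9,375 targeted. Adding the other 750 + 1,500 + 2,400 = 4,650 gives 14,025, and 14,025/60,000 = 23.4%.
- A wide limit, with an assumed 60% uptake in every component: 12,150/0.60 = 20,250, and 20,250/60,000 = 33.8%.

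Tested over population is 20.3% (20.25% before rounding) in both cases.

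**The case against.** The strongest reply is that no information is lost. Coverage and compliance are both to be reported on one denominator, so dividing one by the other gives the share of receivers who swallowed: 0.57/0.60 = 0.95. A reader might infer that delivery failure and failure to swallow cannot be told apart. The article does not support that, because both items are asked and both proportions are defined. This reply stands. It reduces the point to a wrong label on a recoverable quantity, but the label still misleads anyone who reads the compliance figure alone.

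A reader might also take the MDA coverage sentence literally, over all 20 shehias. With 15 assumed low-prevalence, coverage would then be capped at 5/20 = 25%. The article does not mean this. The objectives place MDA coverage in hotspot areas, the coverage surveys are described for hotspot communities and schools, and the compliance sentence that follows names hotspot areas. Only the qualifier is missing from one sentence. The split of 15 and 5 is itself a sample-size assumption, since classification follows the annual surveys.

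On test-and-treat, *targeted* may be loose wording for *tested*. Sample size counts people tested, and no list of people approached but untested is described for stalls or health facilities. Schools and households work from those present, so the article gives little support for absent people counting as covered. It therefore does not establish that coverage will be overstated. What remains is the ambiguity over registered children who return no form or no urine.

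Finally, tablet intake is directly observed, which is stated after the account of school MDA. Receipt and swallowing should then differ little in schools. That is fair, but it also means that the compliance figure there would largely repeat coverage.

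**Conclusion.** The compliance definition does not match its name. As written it is effective coverage, and it understates compliance among receivers by the factor r/n. In the assumed case of 60% receipt and 95% swallowing, it reports 57% instead of 95%. The direction follows from the formula alone whenever some participants did not receive the drug. The size depends on receipt and swallowing rates that the article does not give.

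The two coverage sentences need clarifying and are not established errors. MDA coverage lacks the hotspot qualifier that the rest of the article supplies. Test-and-treat coverage uses a word that could admit untested people. On the plan's own 20% school allowance, the difference would be 23.4% against 20.3%.

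Severity is minor. These are descriptive process measures. They do not enter the primary outcome, the sample size or the rule that classifies shehias, and compliance is not among the listed secondary outcomes.

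**What to change.** Reword three definitions in Statistical methods.

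1. **MDA compliance** (hotspot areas): those who swallowed the drug as recommended, divided by those who reported receiving it. Report separately, as effective coverage, those who swallowed it divided by hotspot survey participants eligible for that round.
2. **MDA coverage:** add that it applies to hotspot areas, to match the objectives and the hotspot section.
3. **Test-and-treat coverage:** replace *targeted* with *tested*, and take the population of the low-prevalence shehias as the denominator, as Sample size already does.

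The compliance change needs no new data, because receipt and swallowing are both asked. The article does not say whether eligibility for MDA is recorded for each participant. If it is not, effective coverage can be given over all hotspot participants with that stated. The only other cost is that test-and-treat coverage may look slightly lower than under a generous reading of the present wording.
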